**Naturopathic Care for Low Back Pain: a Randomized Controlled Trial**

**Clinical Trial Protocol**

|  | **Name** | **Dept./Address** | **Phone No.** | **E-Mail** |
| --- | --- | --- | --- | --- |
| **Trial Design and Consulting** | [name]  [name] | Research  Research | [contact] [name]  [contact] [name] | [contact]  [contact] |
| **Research Co-ordinator** | [name] | Research | [contact] | [contact] |
| **Co-investigator** | [name] | Research | [contact] [name] | [contact] |

Proposed Date of commencement: January 28, 2005

Location of Research: Gateway Canada Post Mail Processing Facility, [name]

Rationale:

The Canadian Union of Postal Workers reports that diagnosed musculoskeletal complaints rose from 53% in 2001 to 59% in 2003. According to Canada Post Corporation's own research, they are experiencing escalating health care costs under their Extended Health Care Plan. Data from the research indicated that musculoskeletal injuries such as sprains, strains, slips, and falls were the most prevalent type of injury from 1994 to 2001 (Canada Post study). Physiotherapy, chiropractic, and massage services accounted for 83% of the total paramedical services used in 2003 (Canada Post study). The purpose of this study is to evaluate the efficacy of Naturopathic treatment on low back pain. This will also lay the groundwork for an assessment of the cost effectiveness of Naturopathic Medicine in the treatment of chronic low back pain in the work place.

Methodology:

Inclusion Criteria:

- mentally competent volunteers 18 to 65, male or female
- low back pain of more than 6 weeks duration
- normal on physical examination at the pre study physical

Exclusion Criteria:

- history of spinal operations
- current history of herniated disk
- current history of systemic rheumatological disease, ankylosing spondylitis, tumors, infection
- pregnancy

Setting and Participants: The setting for this study will be the Gateway Processing Plant of the Canada Post Corporation in Mississauga. The study will take place from January to June, and will involve Canada Post employees and members of the Canadian Union of Postal Workers (CUPW). Workers will primarily be from the Gateway plant, however a minority of the study population will be from other Canada Post facilities. There will be a mix of workers, from day to evening to night shift letter and package sorters, to outdoor letter carriers. The study population will be male and female, in the age groups from 18 to 65.

Sampling and Recruitment: Recruitment for the study will be facilitated by Canada Post Corporation and CUPW representatives. Posters and information sheets will be posted and distributed throughout eligible sites. Interested parties will be encouraged to contact the Naturopathic Doctors directly, either by phone or e-mail and provide their name, phone number, and mailing address. Interested participants will be mailed an Information Kit, which will include: a sample consent form, a Backgrounder explaining the purpose of the study, a description of Naturopathic Modalities, a question and answer sheet regarding the study, contact list and phone numbers of the Naturopathic Doctors, Canada Post, and CUPW representatives involved in the study, the Naturopathic Doctors business cards. Interested participants will be encouraged to ask questions to their Canada Post or CUPW representatives, and Naturopathic Doctors. Following the mailing of the Information Kit, interested participants will be contacted by telephone, and scheduled for a 1 hour initial consultation in a designated room at the Canada Post Gateway Processing Plant. At this consultation, any outstanding questions will be answered by the Naturopathic Doctors, a consent form will be signed and witnessed, and the intake interview and physical exam to evaluate the eligibility for the study, will take place. At the end of the initial consultation, participants will receive the Pain Medication and Pain Therapies Diary chart to complete at home over the next week. Eligible participants will be randomly assigned to either the control or treatment groups, and will be contacted by telephone regarding further appointment times.

At the first visit, prior to any treatments, the Oswestry, Roland and Morris, and SF-36 questionnaires will be completed by the patient to assess baseline. The Pain Medication and Pain Therapies diary will be collected. Both treatment and control groups will receive The Back Booklet, and patients will be instructed to follow the treatments as instructed in the booklet. On subsequent visits, the control group patients will be questioned on the performance of the Book Exercises, and will be encouraged to continue performing them.

The treatment group patients will be positioned prone, and specific acupuncture treatment for low back pain will be applied. During the acupuncture treatment, data on patients’ lifestyle and diet will be obtained, and diaphragmatic deep breathing exercises will be performed. On subsequent visits, the treatment group will continuously receive acupuncture treatment, receive lifestyle and diet counseling, continue to perform deep breathing relaxation techniques, and be encouraged to continue with the exercises as instructed in the exercise booklet.

Intervention arm patients will attend two treatments per week, for a total of 24 treatments over the period of 12 weeks. Control arm patients will receive one initial session with a Naturopathic Doctor, who will give them general advice and exercises as specified in the booklet, and will have bi-weekly visits with the Naturopathic Doctor who will question them on the performance of the Book Exercises, and will encourage the patient to continue performing them.

Both the Intervention and Control arm will complete the Oswestry, Roland and Morris, SF-36, and Perceived Benefit of Treatment questionnaires at 4, 8, and 12 weeks during the study. Both groups will also hand in the Pain Medication and Treatment diary chart, and exercise log at every visit.

Study period is 12 weeks. Clinical evaluations will be performed at:

Baseline (Visit 1 - Day 1)

Interim for the treatment groups: (Visit 2 - Day 7, Visit 3- Day 10, Visit 4 – Day 14, Visit 4 – Day 17, Visit 5 – Day 21, Visit 6 – Day 24, Visit 7 – Day 28, Visit 8 – Day 31, Visit 9 – Day 35, Visit 10 – Day 38, Visit 11 – Day 42, Visit 12 – Day 45, Visit 13 – Day 49, Visit 14 – Day 52, Visit 15 – Day 56, Visit 16 – Day 59, Visit 17 – Day 63, Visit 18 – Day 66, Visit 19 – Day 70, Visit 20 – Day 74, Visit 21 – Day 77, Visit 22 – Day 81, Visit 23 – Day 84, Visit 24 – Day 88, Visit 25 - 91) ie. Monday and Thursday, or Tuesday and Friday.

Interim for the control groups (Visit 2 – Day 7, Visit 3 – Day 21, Visit 4 – Day 35, Visit 5 – Day49, Visit 6 – Day 63, Visit 7 – Day 77, Visit 8 – Day 91)

End of Treatment (Visit 25 - Day 91), Questionnaires and Medication diaries filled in for the last time

Follow-up data will be collected at 6 months post treatment via a mailed questionnaire package containing the Oswestry, Roland and Morris, and SF-36 questionnaires, Perceived Benefit of Treatment scales, as well as the pain killer and adjunctive back pain treatment chart. Non-responders will receive reminders by post. If this is unsuccessful, the patients will be telephoned.

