# Statistical analysis

Randomization will occur using blocked randomization (1:1) and will be conducted using double-observed coin-toss. In the event that the coin should fall, the face up side will be considered the allocation. Heads active, tails control. Participants will not be allocated to any group prior to sequence generation. All analyses will be performed by [name] PhD, a statistician, under blinded conditions. The sample size estimates indicate that a sample of about 36 in each group will be adequate to detect a 10% change in the primary outcome of self-reported pain assuming an intrapatient variability of 15%, a two-sided significance level of 5%, and a power of 80%.

All data will be analyzed according to intention to treat. We will calculate the mean change scores between groups at the specific weeks and the primary endpoint of change from base line to week 12. For any missing data at week 12, we will use LOCF at week 8. Paired t-tests will assess within group changes and two-sample t-tests will compare between groups. All p-values will be exact.

Participants

According to the sample size calculations, 75 participants, randomly allocated to treatment and control group, will take part in this study. Participants will be Canada Post employees, and CUPW union members. Most will be from Mississaugas' Gateway Processing Centre, with a minority coming from Canada Post centers from the surrounding area. Their job function will be varied, ranging from sorting workers to letter carriers. The age range will be workers from 18 to 65 years old.

Recruitment:

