Recruitment for the study will be facilitated by Canada Post Corporation and CUPW representatives. Posters and information sheets will be posted and distributed throughout eligible sites. Interested parties will be encouraged to contact the clinicians directly, either by phone or e-mail and provide their name, phone number, and mailing address. Interested participants will be mailed a Participants Information Kit which will include: a sample consent form, a Backgrounder explaining the purpose of the pilot, a description of Naturopathic Modalities, a question and answer sheet regarding the study, contact list and phone numbers of Naturopathic Doctors, Canada Post, and CUPW representatives, Naturopathic Doctors business cards. Interested participants will be encouraged to ask questions to their Canada Post, CUPW, and Naturopathic Doctors. Interested participants will be contacted by phone, and scheduled for a 1 hour initial consultation in a designated room at the Canada Post Gateway Processing Plant. At this consultation, any outstanding questions will be answered by the Naturopathic Doctors, a consent form will be signed and witnessed, and the intake interview and physical exam will take place. Eligible participants will be randomly assigned to either the control or treatment groups, and will be contacted by telephone regarding further appointment times.

Choosing to withdraw will terminate any further study treatment. Withdrawal will not carry any negative consequences towards the participant from the Naturopathic Clinicians, CUPW or Canada Post Corporation. Participants in the control group that choose to begin treatment will be offered to begin treatment at the conclusion of the trial and we will follow them for an additional 4 weeks.

Risks:

Acupuncture carries with it a minimal risk of infection or organ perforation. All attempts will be made by the Naturopathic Doctors to ensure proper sterile and clean field acupuncture techniques, as specified in the BDDT acupuncture guidelines. Acupuncture points near organs which may be perforated will not be needled. Proper exercise procedures will be initially explained and demonstrated to the patient, but there remains a chance that improper exercise use may harm the patient.

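### As most naturally read, the protocol takes the baseline Oswestry, SF-36 and Roland-Morris after randomisation, so the primary change scores rest on a baseline that allocation could influence

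*Protocol*

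**What the plan says.** The order of events comes from three places in the protocol.

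- **Sampling and Recruitment.** The initial consultation covers questions, consent, intake interview and eligibility examination. The diary is then handed out: "At the end of the initial consultation, participants will receive the Pain Medication and Pain Therapies Diary chart to complete at home over the next"; the period given is one week. Then: "Eligible participants will be randomly assigned to either the control or treatment groups, and will be contacted by telephone regarding further appointment times". The later Recruitment section repeats the order: at the consultation "a consent form will be signed and witnessed, and the intake interview and physical exam will take place", and assignment and the telephone call follow.
- **First-visit procedures (the text after Sampling and Recruitment).** The first visit is when the baseline forms are due: "prior to any treatments, the Oswestry, Roland and Morris, and SF-36 questionnaires will be completed by the patient to assess baseline". The diary comes back on the same occasion: "The Pain Medication and Pain Therapies diary will be collected".
- **Statistical analysis.** "We will calculate the mean change scores between groups at the specific weeks and the primary endpoint of change from base line to week 12". Groups are compared by two-sample t-tests. The only rule tying allocation to another step is that nobody is allocated before the sequence has been generated.

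The Outcomes section names the Oswestry and the SF-36 as primary. Both are completed by the participant. The Roland-Morris is secondary.

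**The concern.** A baseline is protected from allocation only if it is recorded before allocation happens, or at least before anyone involved can know the result. Here the stated condition is that the questionnaires precede treatment, which is weaker.

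Three features make this matter. The participant is the assessor of both primary outcomes. The participant cannot be blinded, since one arm receives acupuncture and the other a booklet with encouragement; only the analysis is described as blinded. And the endpoint subtracts the baseline, so a difference between arms in how the baseline form was filled in enters the treatment contrast directly. Disappointment or hope about the allocation is a plausible cause of such a difference.

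There is also a gap in the data. Someone assigned who leaves before the first visit has no baseline and so no change score. The stated imputation carries week 8 forward to week 12 and cannot supply a missing baseline.

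**Working it through.** **Step 1: is the first visit later than the consultation?** The diary is issued at the end of the consultation, kept at home for a week and collected at the first visit. It cannot be collected at the visit where it was issued, so the first visit is a separate and later one. Assignment and the telephone call are described between the two. The questionnaires therefore follow randomisation on this reading.

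**Step 2: could the arm be known by then?** For the intervention arm, "Intervention arm patients will attend two treatments per week, for a total of 24 treatments over the period of 12 weeks". Control participants attend every two weeks. The listed schedules share Day 1 and Day 7 and first diverge at Day 10 (intervention) against Day 21 (control). A call that books the full calendar would disclose the arm. A call that books only the first dates need not. The protocol does not say which is meant and does not require the arm to be withheld until the forms are complete.

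**Step 3: reproduce the planned sample size.** Inputs from Statistical analysis: difference 10, variability 15, two-sided 5%, power 80%. I read these as 10 and 15 points on the 0 to 100 Oswestry scale, with 15 as the SD of the change score.

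n per arm = 2 × (1.960 + 0.842)² × 15² / 10² = 35.3, rounded up to 36. This agrees with the protocol. Power at 36 per arm is 80.7% by the normal approximation and 79.7% by the non-central t.

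**Step 4: effect of a baseline shift.** Let b be the between-arm difference in reported baseline caused by knowing the arm, and k the fraction of it that persists to week 12. The bias in the change-score contrast is b(1 − k) in size. The figures below take k = 0. Neither b nor k comes from the documents.

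SE = 15 × √(2/36) = 3.54.

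Rejection rate with no true effect = Φ(b/SE − 1.96) + Φ(−b/SE − 1.96). For b = 2, b/SE = 0.566, giving 0.0816 + 0.0058 = 0.087.

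| Shift b (points) | Two-sided type I error | Power for a true 10 points, shift in favour | Power, shift against |
|---|---|---|---|
| 0 | 5.0% | 80.7% | 80.7% |
| 1 | 5.9% | 87.5% | 72.1% |
| 2 | 8.7% | 92.4% | 61.9% |
| 3 | 13.6% | 95.7% | 50.8% |
| 5 | 29.3% | 98.9% | 29.3% |

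With 37 and 38 per arm (the 75 planned participants) and the non-central t, the type I error is 8.8%, 13.7% and 29.6% for b = 2, 3 and 5. The sample size and the approximation make no material difference.

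**The case against.** The strongest counter-argument is that the schedule allows another reading. It lists "Baseline (Visit 1 - Day 1") and gives Day 7 as the next visit in both arms. Day 7 to Day 91 is 84 days, exactly 12 weeks, which would suit a Day 1 without treatment followed by the diary week. If the first visit is that Day 1 and Day 1 is the consultation, the questionnaires could precede assignment. Collection of the diary at the first visit is the stronger evidence against this, but the ambiguity is real and is itself something to reconcile.

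A reader might also infer more than the text supports:

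- **That the call tells participants their arm.** The protocol says only that it concerns appointment times. Disclosure is possible, not stated.
- **That every outcome is affected.** The text fixes the timing of the three questionnaires only. It does not say when baseline weight, BMI, flexion or the pain scale are taken, a physical examination precedes assignment, and the baseline diary is issued before the assignment step.
- **That the trial would be biased towards naturopathic care.** If disappointed controls over-report disability at baseline, their later improvement is exaggerated and the bias runs against the intervention. The raised two-sided error is therefore not a rate of false claims of benefit.
- **That the intention-to-treat set fails.** This would need losses between assignment and first visit. They are possible but not shown, and handling of missing baselines may be left to a SAP.

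The magnitude is also hypothetical. If the reporting shift persists to week 12, it cancels partly or wholly in the change score.

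These limits narrow the claim without removing it. Nothing in the protocol requires the primary baselines to precede randomisation, and no analysis plan can recover a pre-randomisation value that was not collected. Adjusting for baseline would not fully help, because the covariate itself could be affected by allocation.

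**Conclusion.** The point holds in a limited form. On the most natural reading, the baselines of both primary outcomes and of the Roland-Morris are recorded after randomisation and are not protected from knowledge of the arm. That is a weakness in the order of procedures in an open-label trial analysed by change scores. Its actual effect is unknown in size and direction. The rise in type I error to about 9% for a 2-point shift and about 30% for a 5-point shift is an illustration. It rests on assumed shifts that affect baseline and not week 12, an SD of change of 15 points, and 36 to 38 per arm. The documents do not establish that participants learn their arm by telephone or that any shift would occur.

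**What to change.** State in Sampling and Recruitment, in the Recruitment section and in the first-visit procedures that the Oswestry, SF-36 and Roland-Morris are completed at the initial consultation, after consent and confirmation of eligibility. State that a participant is randomised only once the three forms are in hand, and that these values are the baseline in every analysis of those questionnaires. Reconcile the first visit with the Day 1 baseline label, so that it is clear which contact is the consultation and which follows assignment.

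The consultation already takes place, so the change adds no visit and no participants. It does lengthen a one-hour appointment that already holds questions, consent, interview and examination. The documents give no figure for the extra time.

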# Outcomes

Our primary outcome is self-reported low back pain measured by the Oswestry Low Back Pain Disability Questionnaire, and Quality of Life (SF 36). The Oswestry questionnaire characterizes the extent to which low back pain impacts on the participant’s life, work, and daily function and is scored from 0 to 50, or 0% to 100%. The higher the score, the more the low back pain affects life: 0% (no disability) to 100% (totally disabledor bed ridden). The SF-36 questionnaire aims to assess the degree to which specific quality of life measurements are affected by a course of treatment. The higher score indicates improvement in the particular quality of life category.

Secondary outcomes assessed will included self reported pain scale, the Roland Morris Disability questionnaire, forward lumbar flexion range of motion, weight, body mass index (BMI), use of non-steroidal anti-inflammatory Drugs (NSAIDS) and use paramedical interventions. All measures will be assessed at baseline, weeks 4, 8 and 12. We will assess the construct validity of the Oswestry with the the Roland Morris Disability questionnaire and assume good correlation (>0.5). We will ask for self-reported adherence to the regimen, adverse events, and perceived benefit (Naturopathic care group only) at the same time periods.

Adherence with treatment will be monitored on a semi-weekly basis using a percentage compliance scale, with <70% adherence considered non-compliant at each time point. This is a strategy we previously assessed in the HIV/AIDS field.

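### Two instruments are named as the primary outcome but the trial is sized for one, so the stated 5% error and 80% power cannot both be assured at 36 per group

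*Protocol*

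**What the plan says.** The Protocol, Outcomes, states: "Our primary outcome is self-reported low back pain measured by the Oswestry Low Back Pain Disability Questionnaire, and Quality of Life (SF 36"). The sentence is in the singular but names two instruments. The Oswestry is scored 0 to 50, or 0% to 100%. Of the SF-36 the section says "The higher score indicates improvement in the particular quality of life category", so it yields more than one score, and none is picked out as primary. The next paragraph begins "Secondary outcomes assessed will included self reported pain scale, the Roland Morris Disability questionnaire", so a separate pain scale is secondary.

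The Protocol, Statistical analysis, gives about 36 per group as enough to "detect a 10% change in the primary outcome of self-reported pain", "assuming an intrapatient variability of 15" per cent, with "a two-sided significance level of 5%, and a power of 80" per cent. It refers to one primary endpoint, the change from baseline to week 12, and plans two-sample t-tests between groups. It gives no split of the significance level, no order of testing, and no statement of whether one or both instruments must succeed.

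**The concern.** The two sections do not fit together: one has two primary instruments, the other a single sized primary outcome. Error rate and power both depend on how two primary results are combined, and the Protocol does not say. A sponsor could later call the trial positive on the Oswestry alone, on the SF-36 alone, on one SF-36 category, or only on both. Each of these rules has a different false-positive rate and a different power, and the choice could be made after the data are seen.

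A lesser problem is the label in the sample-size sentence. It speaks of self-reported pain and does not name the Oswestry, although a self-reported pain scale is listed among the secondary outcomes.

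**Working it through.** **Inputs.** From the Protocol, Statistical analysis: difference 10 (read as 10 points on a 0–100% scale), SD 15 (the stated variability, taken as the SD of the compared score), two-sided 5%, power 80%, 1:1 allocation, about 36 per group. Not in the Protocol, so assumed: the correlation between the test statistics (0 to 0.7), the number of SF-36 scores tested, and the size of effect on the SF-36.

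**1. The plan's own figure, one outcome.**
n per group = 2 × (1.960 + 0.842)² × (15/10)² = 35.3, rounded up to 36. The exact t-test calculation gives 37. Power at 36 per group is 80.7% by the normal approximation and 79.7% by the t-test. The stated figure reproduces.

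**2. Either instrument counts, each tested at 5%.**
For m independent tests, familywise error = 1 − 0.95^m. For correlated tests it was simulated with equally correlated normal statistics (1,000,000 draws).

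| Tests | Independent | Correlation 0.5 | Correlation 0.7 |
|---|---|---|---|
| Oswestry + 1 SF-36 score (m = 2) | 9.75% | 9.1% | 8.3% |
| Oswestry + 2 scores (m = 3) | 14.3% | 12.5% | 10.9% |
| Oswestry + 8 scores (m = 9) | 37.0% | 26.8% | 20.1% |

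The first row fits the two instruments as named. The other rows illustrate what happens if the SF-36 is read category by category.

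**3. Either instrument counts, Bonferroni at 0.025 each.**
The expected test statistic at 36 per group is 10 / (15 × √(2/36)) = 2.828. The power for each outcome is Φ(2.828 − 2.241) = 72.1%, or 70.4% by the t-test. To restore 80% for each outcome takes 43 per group (45 by the t-test).

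The chance that at least one of the two succeeds is higher if the SF-36 has the same standardised effect. It is 1 − (1 − 0.721)² = 92% if the tests are independent. At correlation 0.7, where both succeed with probability 0.616, it is 2 × 0.721 − 0.616 = 83%. The Protocol states no effect for the SF-36, so it does not support that figure. If only the Oswestry responds, power is about 70%.

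**4. Both instruments must be significant, each at 5%.**
No adjustment of the level is needed, and the error stays at or below 5%. Joint power at 36 per group is the bivariate normal probability that both statistics, each with mean 2.828, exceed 1.960, assuming the same standardised effect on the SF-36:

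| Correlation | Joint power |
|---|---|
| 0 | 65.2% |
| 0.3 | 67.7% |
| 0.5 | 69.7% |
| 0.7 | 72.2% |

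**5. What the sample-size label refers to.**
Outcomes describes the Oswestry result as self-reported low back pain and as primary. Statistical analysis sizes "a 10% change in the primary outcome of self-reported pain", also called primary, and a percentage fits the Oswestry's 0–100% scoring. The Oswestry is the likelier meaning, but the secondary pain scale carries nearly the same name.

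**The case against.** The strongest reply is that a testing order, a split of the significance level and the choice of SF-36 score are commonly left to a statistical analysis plan, which is not shown here. Their absence alone would not be a finding, and that much stands. What remains is a conflict within the Protocol: two instruments under the primary outcome in one section, one sized primary outcome in the other. Which outcome is primary and which one the sample size covers are choices that the Protocol itself makes, and it makes them inconsistently.

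Three stronger readings are tempting, and the text does not support them.

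- A reader might infer that the 5% error rate fails. It fails only if either instrument counts and each is tested at 5%. The 5% level appears only in the sample-size sentence, and no level is attached to the t-tests. If both instruments must succeed, the error rate holds and power is what suffers.
- A reader might take 37% as the error rate. That needs nine tests, a number the Protocol does not give, and independence, which is implausible for scores from the same patients. For the two named instruments the figure is about 8–10%.
- A reader might infer that the trial was sized on a secondary outcome, because the Protocol says "Secondary outcomes assessed will included self reported pain scale". The sized outcome is called primary, and its label nearly matches the one given to the Oswestry. This is an ambiguity of wording only.

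It is also fair to say that keeping two primary outcomes is legitimate if the rule is stated and the power is restated to match.

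**Conclusion.** The point holds as an inconsistency about which outcome is primary and what the sample size covers. The 36 per group is right for one outcome and is not criticised. With two primary instruments and no combining rule, the stated 5% and 80% are not both assured:

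- either counts, unadjusted: error about 8–10%, rising to 12.5–14% with two SF-36 scores and 27–37% with eight (correlation 0.5 to 0);
- either counts, Bonferroni: error 5%, power about 70% for each outcome;
- both required: error at most 5%, joint power about 65–72%.

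These figures rest on the Protocol's 10 and 15, on correlations of 0 to 0.7 between the tests, on an assumed number of SF-36 scores and, for joint power, on an SF-36 effect of the same standardised size. The Protocol gives none of the last three.

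**What to change.** Make the change in Oswestry score (0–100%) from baseline to week 12 the single primary outcome, and name the Oswestry in the sample-size sentence. Name one SF-36 score and test it at 5% only if the Oswestry is significant. This fixed sequence keeps the overall error for the two tests at 5%. Report the other SF-36 scores as secondary, without confirmatory claims. The pain scale stays secondary, as now.

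The sample size does not change, since 36 per group was computed for one outcome. The real cost is that the SF-36 loses its co-primary status, so a benefit on quality of life alone could no longer make the trial positive.

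If the sponsor prefers to keep both as primary, the Protocol should name the SF-36 score, say whether either or both must be significant, and restate the power at 36 per group: about 70% for each outcome with a Bonferroni split (43 to 45 per group would restore 80%), or about 65–72% if both must succeed, with the SF-36 effect assumption written down.
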